### Passive Control Condition

Participants will receive the usual Advantage Dental Services practices, which may include receiving information about dental benefits via telephone and mail. This group will be on a waiting list for the trial intervention for 9 months and will then receive one toothbrushing kit. Only children less than 36 months old and their families will be included in this control condition.

By the conclusion of the study, all families will have received toothbrushing supplies. This principle, that all eligible Advantage Dental Services members will have the opportunity to benefit, is part of the organization’s mission.

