### Statistical Analysis

#### Sample Size

Sample size for dental care outcomes was not calculated, as the sample size of 20,000 participants was deemed sufficient to observe an effect of the intervention on the primary outcome of restorative care utilization.

Prevalence and effect size estimates for frequency of twice daily toothbrushing among children less than 36 months old at baseline was based on that reported in a study in a similar population [25]. Assuming a proportion in the passive control group of .6, alpha = .025, beta = .20, the required sample sizes for effect sizes of 50% and 40% are 39 and 66 participants in each group. We decided on a sample size of 150 participants in each group.

Untreated dental caries estimate was based on that reported in a study in a similar population [1]. Assuming a proportion of children with dental caries experience in the passive control group of .5, alpha = .025, beta = .20, the required sample sizes for effect sizes of 30% and 40% are 206 and 113. We decided on a sample size of 210 participants in each group.

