#### Statistical Analysis Plan

Descriptive statistics (means, SD, counts, and percentages) will be calculated for all variables of interest overall and stratified by age group. Difference in difference models will be used to evaluate changes in frequencies and rates for pre versus post intervention effects within the intervention groups and for passive control versus active control versus test effects. Linear regression will be used to evaluate continuous outcomes and logistic regression will be used to evaluate binary outcomes. The primary hypothesis for all participants is that the test intervention group will have a lower number of restorative dental care procedures received than the active control group during the 18 months post intervention start date. For children less than 36 months old, the primary hypothesis is that the test intervention will increase toothbrushing frequency more than the active control intervention and no change in passive control group will be observed 10 months post intervention start date. Secondary hypotheses are that member satisfaction and oral health-related quality of life of the participants will be greater and that dental care costs and dental caries will be lower in the test intervention and active control than in the passive control.

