## Results

### Timing of Recruitment, Intervention Delivery, and Follow-Up

Participants were recruited in June 2014, and the intervention is being delivered from August 2014 through April 2015. The toothbrushing supply kits were sent in August and November 2014 and February 2015. Postcards and telephone messages are being delivered to the test intervention group from August 2014 through April 2015. The helpline and other telephone services to request additional supplies are available throughout the intervention period, from August 2014 through April 2015.

Baseline interviews with the subsample of 450 parents/caregivers of children less than 3 years old have been conducted in June and July 2014, and final interviews will be conducted in May 2015. Dental claims data for all participants will be extracted in August 2015. Clinical examination of the subsample will be conducted in July 2016.

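### The primary brushing hypothesis includes an unmargined claim of no change in passive control, and the plan does not fix whether the passive kit comes before or after the final interview.

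*Protocol article*

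**What the plan says.** The Statistical Analysis Plan section gives one primary hypothesis for children under 36 months, in two parts. The first is that "the test intervention will increase toothbrushing frequency more than the active control intervention". The second is that "no change in passive control group will be observed 10 months post intervention start date". The same section plans the analysis: "Difference in difference models will be used to evaluate changes in frequencies and rates for pre versus post intervention effects within the intervention groups", and also for comparisons among the three arms. It gives no margin within which a change in passive control would count as none.

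The Sample Size section designs for detecting a difference: "Assuming a proportion in the passive control group of .6, alpha = .025, beta = .20", and "the required sample sizes for effect sizes of 50% and 40% are 39 and 66 participants in each group". It then settles the number: "We decided on a sample size of 150 participants in each group".

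On timing, the Passive Control Condition section puts these families on a "waiting list for the trial intervention for 9 months and will then receive one toothbrushing kit". The section on timing of recruitment, delivery and follow-up runs the intervention from August 2014 through April 2015 and says "final interviews will be conducted in May 2015". The clinical examination is in July 2016. The Toothbrushing Kit section says that each kit includes an instruction sheet telling families to brush twice a day.

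**The concern.** There are two separate problems.

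**A null claim inside a primary hypothesis.** Without a margin, the only evidence that a standard analysis can offer for the passive clause is a non-significant pre-post change. That result also arises when the change is real but the arm is too small to show it. The clause can therefore appear confirmed because the estimate is imprecise. A reader could also treat a movement in passive control as counting against the program, although it says nothing about test versus active.

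**Unfixed order of kit and outcome.** The kit supplies the materials and the instruction for the very behavior that the final interview measures. If some passive families receive it first, their reported brushing may move towards that of active control, and contrasts with passive control shrink. Those contrasts matter: the main research question in Aims and Objectives includes a no-intervention comparator, and the brushing sample size is anchored on the passive proportion.

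**Working it through.** **1. The plan's own figures.** Inputs from Sample Size: control .6, alpha .025, power 80%, relative effects of 50% and 40% (that is, .90 and .84). Sidedness is not stated. With the pooled-variance formula, two-sided, no continuity correction:

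n = [z(α/2)·√(2p̄(1−p̄)) + z(power)·√(p1(1−p1)+p2(1−p2))]² / (p2−p1)²

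- .6 vs .90: (2.241×√0.375 + 0.842×√0.33)² / 0.09 = 38.3, so 39.
- .6 vs .84: (2.241×√0.4032 + 0.842×√0.3744)² / 0.0576 = 65.2, so 66.

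Both reproduce. The arithmetic is sound, but it sizes the study to find a difference, not to show that there is none.

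**2. Precision of the change within passive control.** Inputs: n = 150 and rate .6 from Sample Size. The pre-post correlation ρ is not given, so 0.2 to 0.5 is assumed.

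SE = √(2 × 0.6 × 0.4 × (1−ρ) / 150)

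| ρ | SE | 95% half-width | Power for a true 10-point rise | Missed |
|---|---|---|---|---|
| 0.2 | 0.0506 | 0.099 | 0.51 | 49% |
| 0.3 | 0.0473 | 0.093 | 0.56 | 44% |
| 0.5 | 0.0400 | 0.078 | 0.71 | 30% (0.295) |

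Power is Φ(0.10/SE − 1.96), two-sided 5%. Letting the variance follow the raised rate changes little: 41% missed at ρ = 0.3 and 27% at ρ = 0.5. On that basis, at the plan's only stated alpha, .025 taken two-sided, the figures are 52% and 37%. A true 5-point rise, at two-sided 5%, would be missed with probability 0.81 at ρ = 0.3 and 0.755 at ρ = 0.5.

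**3. If no change were tested properly.** Two one-sided tests at 5%, true change zero: power = 2Φ(m/SE − 1.645) − 1 for margin m, or zero where that is negative.

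- Margin of 10 points: 36% at ρ = 0.3 and 61% at ρ = 0.5. For 80% power, 288 and 206 families would be needed.
- Margin of 5 points: zero at both correlations.

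**4. The calendar.**

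- August 2014 + 9 months = May 2015: the wait ends and the kit is due.
- Final interviews: May 2015.
- August 2014 + 10 months = June 2015, the endpoint as labelled; May 2015 is the tenth calendar month if August is counted as the first.
- May 2015 to July 2016 = 14 months from the kit falling due to the clinical examination.

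The kit may come before, during or after the interviews. If it comes first, exposure before interview is a matter of weeks. If a share f of passive families hold the kit at interview and it has by then raised twice-daily brushing among them by δ, contrasts with passive control shrink by f × δ. The documents give neither quantity.

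**The case against.** The best defense is that the clause describes an expected pattern, not a test. No decision rule says that test versus active fails if passive control moves, and none says that non-significance confirms anything. The planned difference-in-difference model compares changes between arms, and test versus active does not use the passive arm. This stands, and it limits the damage. It does not justify the clause, which is worded as part of the primary hypothesis and which the planned data could not confirm.

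It can also be said that the miss rates describe a stand-alone pre-post test that the plan does not name as confirmatory. That is fair. They show what a non-significant change would be worth, not the power of a planned primary test.

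On timing, the sections allow the interview to come first. Delivery ends in April 2015, Data Collection places interviews at the end of the intervention, and the kit has no calendar date. A condensed article may leave mailing details to the full protocol. The sections therefore do not contradict each other outright. But the article does state a 9-month wait and a 10-month endpoint, and taken literally these put the kit first.

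Two stronger readings are tempting and are not supported. A reader might infer that growing older makes no change in passive control implausible. The documents give no age trend in brushing, and a trend shared by all arms cancels in the difference-in-difference comparison on the model's scale. A reader might also infer that the outcome is certainly measured after the kit; the order is only left open. The delayed kit itself is openly disclosed as a waiting-list feature. The 18-month restorative-care hypothesis is test versus active only, so it raises no issue here.

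**Conclusion.** The concern holds in a limited form. A primary hypothesis contains a claim of no change without a margin, and with 150 passive families a non-significant result could not establish it: half-width 8 to 10 points, and 30% to 49% of true 10-point rises missed. Those figures rest on the plan's rate of .6, complete follow-up of 150 families, an assumed correlation of 0.2 to 0.5, and a two-sided 5% test.

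The order of passive kit and final interview is unfixed. Any resulting bias is towards no effect, is confined to contrasts with passive control, and cannot be sized from the documents. The test-versus-active contrast is affected by neither problem, and nothing in the plan makes it fail because passive control moves.

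**What to change.** 1. **Hypotheses.** Remove the no-change clause. State the brushing hypotheses as between-arm differences in change from the planned difference-in-difference model: test versus active, and each versus passive. Say which are primary, bearing in mind that Sample Size takes its starting rate from the passive group.
2. **Timing.** Reconcile the Passive Control Condition, Statistical Analysis Plan and timing sections so that each passive family's final interview is completed before its kit is mailed. Record both dates for every passive family, so that any reversal of order can be seen.
3. **Labelling.** At the 24-month examination, describe the passive arm as having received a delayed single kit, not as having had no intervention.

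The cost is a change of wording, plus the sequencing of interviews and mailing for 150 families. No new data or larger sample is needed.

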### Study Measures and Data Collection

#### Outcomes

The primary outcome for all children less than 21 years old will be restorative dental care received as a proxy for the presence of dental caries. Additionally, for children less than 36 months old at baseline, the other primary outcome will be parent/caregiver reported frequency of twice daily toothbrushing the child’s teeth. Secondary and tertiary outcomes will be cost of dental care for all participants; and, only for children less than 36 months old at baseline, parent/caregiver-reported oral-health related quality of life of the child, satisfaction with the program, and dental caries (tooth decay).

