#### Data Collection

Data on type, amount, and cost of dental care will be collected through health information systems of the dental care organization (Enrollment and Claims Database) for all participants. For children less than 36 months old, information on the children’s toothbrushing behaviors, parent-rated oral health and oral health-related quality of life of the child, child’s juice consumption and frequency, parental self-efficacy, intention and attitudes regarding brushing the child’s teeth, parent educational level, and their opinions about each component of the intervention will be collected through telephone interviews with parents/caregivers at baseline and at the end of the intervention. For children less than 36 months old at baseline, information on the presence of untreated dental caries (cavitated caries in permanent or primary teeth) will be collected through a clinical examination 24 months after the study start date. Fidelity information will be obtained through examination of internal records of mailings, returned mail receipts, and telephone calls.

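### The satisfaction hypothesis sets test and active control against a waiting-list arm that has at most one recent kit to rate

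*Protocol article*

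**What the plan says.** Four sections of the protocol article bear on this.

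- **Statistical Analysis Plan:** "Secondary hypotheses are that member satisfaction and oral health-related quality of life of the participants will be greater". The only comparator the sentence gives is at its end: "in the test intervention and active control than in the passive control".
- **Outcomes:** among the outcomes for children under 36 months at baseline, the article lists "satisfaction with the program". It is grouped under secondary and tertiary outcomes, without saying which of the two it is.
- **Data Collection:** after a list of behaviours, parent-rated oral health and parental attitudes, the interview content ends with "their opinions about each component of the intervention will be collected through telephone interviews with parents/caregivers at baseline and at the end of the intervention". No item on satisfaction with the dental organization is listed.
- **Passive Control Condition:** "Participants will receive the usual Advantage Dental Services practices, which may include receiving information about dental benefits via telephone and mail". Then: "This group will be on a waiting list for the trial intervention for 9 months", after which the group gets one toothbrushing kit.

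**The concern.** A comparison of satisfaction between arms needs something that respondents in every arm can rate. The outcome is satisfaction with the program, but the hypothesis uses as its reference the arm from which the program is withheld during the evaluation period.

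If passive parents are asked about the program, their answers concern either nothing yet received or a single new kit. A difference in favour of test or active control would then say little about how well the program was liked. It would mostly show that some families had been sent something and others had not, or not yet. The Discussion says the evaluation will be used to judge whether the intensive instruction and social support are needed. For satisfaction, the comparison that informs that decision is test versus active control, and the hypothesis does not name it.

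**Working it through.** The plan gives no power, effect size or sample size calculation for satisfaction, so there is no figure to reproduce. The check sets arm content, calendar and outcome definition side by side.

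**1. What each arm has to rate at the final interview.** Arm content comes from Components of the Intervention, The Toothbrushing Kit, Active Control Condition and Passive Control Condition. Mailing dates come from Timing of Recruitment, Intervention Delivery, and Follow-Up.

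| Component | Test | Active control | Passive control |
|---|---|---|---|
| Kits | 3 (August and November 2014, February 2015) | 3 (same dates) | 0 or 1 |
| Supplies helpline | yes | yes | not during the wait |
| Postcards | yes | no | no |
| Automated calls | yes | no | no |
| Advice helpline | yes | no | no |

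Test families can rate five components and active control families two. Passive families can rate none while waiting and, once the wait is over, one kit.

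**2. Calendar.** Delivery runs from August 2014 through April 2015: 5 months in 2014 plus 4 in 2015 gives 9 months. Assume the passive wait is counted from the start of delivery, which the article implies but does not state. The wait then ends around the turn of April to May 2015, and final interviews are in May 2015. The kit may arrive just before or just after the interview. If the wait were instead counted from recruitment in June 2014, it would end around March 2015 (June plus 9 months), and the passive family would still have only one kit, received late. Under either count the passive arm has at most one recent kit.

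**3. Object of the rating.** If the kit comes after the interview, passive parents have no program component to rate. If it comes before, they rate one recent kit, while active control parents rate three kits and a supplies line used over 9 months, and test parents rate those plus three further components. In neither case do the arms rate the same thing.

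**4. Extent.** The hypothesis implies two satisfaction contrasts, test–passive and active–passive, and both are affected. The interviews number 450, with 150 per arm (Trial Status), so the passive third (150/450) is the part in question. Test versus active, 150 against 150, has two components in common and is not affected.

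**5. The rest of the sentence.** Quality of life, dental costs and caries do not depend on having received the program, so this point does not touch the passive contrasts for them.

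**The case against.** The strongest reply is that the hypothesis speaks of member satisfaction, and that elsewhere in the article a member is someone enrolled with the dental organization. Passive families are members and receive the organization's usual services, so they could rate those, and a three-arm contrast would be well defined. That is a fair reading of the word. However, the Outcomes section names a different construct, and Data Collection lists "their opinions about each component of the intervention" but nothing about the organization. The article condenses the questionnaire, so an arm-neutral item may exist. Even then, the Outcomes section and the hypothesis name different things, and one of them has to change.

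Three stronger readings are tempting, and the document does not support them.

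- **That the hypothesis cannot be tested at all, or that all 150 passive interviews are without a valid rating.** The passive kit may arrive before the interview, and a kit can be rated. The fault is that the ratings are not of like things, not that none can exist.
- **That the difference-in-difference model fails for this outcome.** No arm had received the program at the June–July 2014 baseline, so a change score for program satisfaction would have little meaning. But the plan ties those models to frequencies and rates and also provides for linear and logistic regression. A regression on the final interview alone is compatible with the text.
- **That a favourable result would be presented as a confirmed hypothesis.** The article promises publication whatever the outcome and says nothing on how this result would be worded.

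**Conclusion.** The point holds as an inconsistency between the outcome definition, the content of the passive arm and the stated comparison. As defined, program satisfaction in the test and active arms is set against an arm with at most one recent kit, and any difference would largely reflect having received something.

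Its weight is small. It affects both satisfaction contrasts against the passive arm, and no primary outcome, primary hypothesis or sample size.

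The conclusion assumes that the Outcomes section defines what is measured, and that the component opinions are the satisfaction data, which the article suggests but does not state outright. If an organization-level item was asked in all three arms, the contrast is sound and the error lies in the outcome definition instead.

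**What to change.** Which edit applies depends on what was intended.

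- **If program satisfaction was meant:** in the Statistical Analysis Plan section, take the passive arm out of the satisfaction hypothesis. Compare test with active control at the final interview on the components both receive, the kit and the supplies helpline. Describe ratings of the postcards, automated calls and advice helpline within the test arm only.
- **If satisfaction with the dental organization was meant, and is asked in all arms:** correct the Outcomes section to name that outcome, and keep the three-arm contrast.

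Under either option the passive contrasts for quality of life, costs and caries stay as they are.

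The cost is a one-sentence edit in one section or the other. Under the first option one secondary claim is dropped and one test–active comparison is added, which should be declared as an addition. Under the second the outcome is redefined. Neither option needs new data, provided the items described were asked.

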### Data Management and Quality Assurance

Advantage Dental Services staff members will collect the data. Interview responses will be entered in a secure and US Health Information Portability and Accountability Act of 1996 compliant database with range checks for data values.

### Ethics and Dissemination

The results from the trial will be published regardless of the outcome. Reporting of this trial will adhere to the relevant and most up-to-date CONSORT statement [19] and its relevant extensions [20]. The investigators will ensure that the trial is conducted in compliance with this protocol and federal regulations.

## Results

### Timing of Recruitment, Intervention Delivery, and Follow-Up

Participants were recruited in June 2014, and the intervention is being delivered from August 2014 through April 2015. The toothbrushing supply kits were sent in August and November 2014 and February 2015. Postcards and telephone messages are being delivered to the test intervention group from August 2014 through April 2015. The helpline and other telephone services to request additional supplies are available throughout the intervention period, from August 2014 through April 2015.

Baseline interviews with the subsample of 450 parents/caregivers of children less than 3 years old have been conducted in June and July 2014, and final interviews will be conducted in May 2015. Dental claims data for all participants will be extracted in August 2015. Clinical examination of the subsample will be conducted in July 2016.

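### The primary outcome counts 18 months of restorative procedures, but the only stated claims extraction falls about 12 months after the intervention start

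*Protocol article*

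**What the plan says.** All statements are in the protocol article.

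- **Outcome.** The Outcomes section makes restorative dental care received the primary outcome for every child under 21.
- **Window.** The Statistical Analysis Plan section states the primary hypothesis for all participants: the test group will have a "lower number of restorative dental care procedures received than the active control group during the 18 months post intervention start date".
- **Source.** The Data Collection section names one source: "Data on type, amount, and cost of dental care will be collected through health information systems of the dental care organization", that is, its enrollment and claims database.
- **Start.** The section on timing of recruitment, intervention delivery and follow-up says that "the intervention is being delivered from August 2014 through April 2015". It confirms the starting month with the mailings: "The toothbrushing supply kits were sent in August and November 2014 and February 2015".
- **Extraction.** The same section gives one date for this source: "Dental claims data for all participants will be extracted in August 2015". It mentions no earlier, later or repeat extraction.

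**The concern.** The window and the extraction date are both stated outright, and they do not fit. An 18-month count from August 2014 needs claims up to February 2016, and an extract taken in August 2015 stops about six months short of that.

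The outcome affected is the primary one for the whole trial, and it has no other stated source. A team that follows the timetable literally would analyse roughly the first year and could not report the hypothesis as worded. If the conflict is left unresolved, the choice between a 12-month and an 18-month count stays open and could be made after the data have been seen. Cost of dental care comes from the same database, so the extraction date limits that outcome too. The article states no window for cost, so there is no contradiction on that outcome.

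**Working it through.** **Inputs (protocol article)**

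- Intervention start: August 2014 (timing section; first kits mailed that month).
- Primary window: 18 months from the start (Statistical Analysis Plan section).
- Claims extraction: August 2015 (timing section).
- Days within these months: not given, so each is varied from the first to the last day.

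**Step 1: where the window ends.** August 2014 + 18 months = February 2016.

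**Step 2: what the extract covers.** August 2014 to August 2015 = 12 months nominally. Shortfall = 18 − 12 = 6 months, and 6/18 = 33%.

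**Step 3: allow for the unstated days.** Share outside the extract = 1 − (days covered / days in window).

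| Start | Extraction | Days in window | Days covered | Share outside |
|---|---|---|---|---|
| 1 Aug 2014 | 1 Aug 2015 | 549 | 365 | 1 − 365/549 = 34% |
| 1 Aug 2014 | 31 Aug 2015 | 549 | 395 | 1 − 395/549 = 28% |
| 31 Aug 2014 | 1 Aug 2015 | 547 | 335 | 1 − 335/547 = 39% |
| 31 Aug 2014 | 31 Aug 2015 | 547 | 365 | 1 − 365/547 = 33% |

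The extract therefore covers about 11 to 13 months, and 28% to 39% of the window lies outside it.

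**Step 4: would another starting point rescue the date?** Counting from recruitment in June 2014 gives 14 months to August 2015, still short of 18.

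**Step 5: is the calendar only loosely worded?** The other timed items were checked from 1 August 2014.

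- Delivery ends in April 2015. The end of that month is month 9, and the stated intervention period is 9 months.
- Final interviews are in May 2015. The end of that month is month 10, and the hypothesis says "no change in passive control group will be observed 10 months post intervention start date".
- Clinical examinations are in July 2016. The end of that month is month 24, and caries data "will be collected through a clinical examination 24 months after the study start date".

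All three fit. Only the claims extraction does not.

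**Step 6: claims lag.** The article gives no lag between treatment and a complete claim. Any lag widens the gap. If it were 1 to 3 months (an assumption), the nominal 12 months would hold 11 to 9 complete months, or 11/18 = 61% down to 9/18 = 50% of the window.

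**Step 7: is there time to correct it?** From February 2016 to June 2017, taken as early summer, is 16 months.

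**The case against.** The strongest reply is that nothing is really lost. The outcome sits in a standing administrative database, not in study visits, and an early extract does not destroy later records. The article does not call August 2015 the final extraction, and with results due in early summer 2017 a later one may well be intended. This part stands. A reader might infer that the last six months of data will be missing, or that the outcome cannot be obtained at all. The documents show only that those months fall outside the one extract described. The contradiction remains, because no second extract is mentioned. Condensing a protocol into an article can explain an omission, but not two stated dates that disagree.

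A second reply is that the extraction date may be right and the 18 months wrong. The article does not settle this, so the repair must allow for either.

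A third is that the cut falls on the same calendar date in the test and active control arms. That also stands: the comparison loses events and has a shorter horizon, but no arm is evidently favoured.

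Two stronger readings are tempting and lack support:

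- **A definite loss of power.** The Sample Size section says that no calculation was made for dental care outcomes. Any figure would need an invented starting power and an assumed variance for procedure counts. With 10,797 and 10,796 families in the two arms, the true power could be high or low.
- **The largest effect in the final six months.** Delivery ends in month 9, and the Introduction says that brushing habits persist but need reinforcement. The effect could grow or wane after that, and the article does not say which.

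**Conclusion.** The point holds as an internal contradiction. The primary window runs to February 2016, the only stated extraction is in August 2015, and the two differ by about six months. Followed as written, about a third of the primary window (28% to 39%, depending on the unstated days) would be outside the extracted data, before any claims lag.

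This rests on the window being counted from the August 2014 start, as the hypothesis says, and on August 2015 being the only extraction, as the text reads. It does not rest on any assumed lag or event rate. The consequence is a truncated primary outcome and a window left open to choice. Actual loss of records, bias toward one arm and a particular fall in power are not shown. It should be corrected because it concerns the trial-wide primary outcome and the correction is cheap.

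**What to change.** **Preferred if 18 months is intended.** Move the extraction for the primary outcome, or add a second one, to after the end of February 2016 plus a fixed claims run-out. State the length of the run-out, and select procedures by date of service. Extracting alongside the July 2016 examinations works only if the run-out is about 4 to 5 months or less, because the end of February to July 2016 is 4 months at the start of July and 5 at its end. A longer run-out needs a later date, and there is room for one before early summer 2017. An August 2015 extract can then be kept as a data check, not used for the primary comparison.

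**If August 2015 must stand as the only extraction.** Restate the primary window as about 12 months, shortened by whatever run-out is fixed, and do so before any outcome data are seen. The cost is a shorter primary outcome.

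Either way, the Statistical Analysis Plan section and the timing section must give the same window. The first option costs a changed or added date, a run-out length and a service-date rule. It uses the existing database, needs no new contact with families and does not delay the stated results date.
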